## Abstract

**Background:**

Therapies that significantly improve the neurological and functional recovery of individuals with spinal cord injury (SCI) are still urgently needed. The ketogenic diet (KD) has been shown to improve forelimb motor function in an SCI rat model, likely by reducing inflammation and cell death in the spinal cord. Furthermore, our recent pilot study in patients with SCI showed that, compared with a standard hospital diet (SD), 5 weeks of KD started during acute care improved upper extremity motor function and reduced serum levels of a neuroinflammatory blood protein. The primary goals of the current study are to: 1) show the safety and feasibility of administering a KD during acute care for SCI; 2) determine if consuming 5 weeks of a KD significantly improves motor and sensory functions, functional independence and glycemic control; and 3) quantify serum biomarkers that are linked to improvements in neurological recovery and functional independence via targeted proteomics.

**Methods/design:**

In a single-masked, longitudinal, randomized, parallel-controlled study, a total of 60 eligible, acutely traumatic spinal cord injured (cervical 5 to thoracic 12) participants ranging in age from 18 to 60 years with American Spinal Injury Association impairment scale (AIS) grades A–C (AIS-A, sensorimotor complete; AIS-B, sensory incomplete/motor complete; and AIS-C, nonfunctional motor incomplete) are being enrolled. Neurological and functional examinations, resting energy expenditure, blood, urine, and stool collections, and protein analyses related to neurological recovery will be performed within 72 h of injury (baseline measure) and repeated after 5 weeks of KD or SD (discharge measure). We anticipate a completion rate of 80% with a total of 48 participants.

**Discussion:**

Intervention with a more neuroprotective diet during acute care of SCI can be implemented anywhere in the world at low cost and without major regulatory hurdles. Better functional recovery will lead to a better quality of life and long-term health outcomes in individuals with SCI. While this study targets SCI, if successful it has the potential to improve neurological outcomes for individuals with various traumatic injuries.

**Trial registration:**

NCT03509571 Registered on April 28, 2018.

## Background

Despite advances in understanding the basic neurobiology of spinal cord injury (SCI), the development of therapeutic strategies for the acutely injured spinal cord has been agonizingly slow. Thus, SCI remains a significant cause of disability and mortality. SCI in humans not only leads to the well-recognized loss of motor and sensory function, but also the less-studied multiple secondary complications (i.e., bladder and bowel dysfunction, metabolic disorders and cardiovascular disease) caused by extreme physical inactivity due to paralysis [1–3]. These secondary complications of SCI contribute to the greatly reduced lifespan of these patients, which is rarely emphasized. While the field has made large strides in improving the survival of individuals with SCI in the acute 2-year phase after injury (40% reduction in mortality), there have been no gains in lifespan in the chronic situation over the last 20 years [4]. Furthermore, individuals with SCI who survive beyond the first 2 years after injury still die on average 13–25 years earlier than able-bodied people, depending on the level and severity of injury [4–6]. The current paradigm holds that better neurological recovery during the acute period will lead to a longer, more active and independent life for individuals with SCI. In addition, individuals with improved neurological recovery are expected to better manage problems such as spasticity, weight gain and chronic pain, and to be less likely to experience feelings of anxiety, loneliness and depression.

After the initial trauma of SCI, cell death and tissue loss continue for several weeks [7], a window in which one could effectively intervene with neuroprotective strategies. During this time, an escalating cycle of glutamate excitotoxicity, inflammation and neuronal apoptosis leads to progressive degeneration in the spinal cord [8]. Currently, the only approach taken to restrict secondary damage after SCI is surgical decompression and the administration of methylprednisolone. However, the recommendations to use methylprednisolone have fluctuated from “standard of care” to “optional” to “not recommended” and currently back to “optional” in the US and Canada since it has been shown to offer merely marginal benefit in select patient groups and increase the risk of major complications—in particular, gastrointestinal ulcers/bleeding during the acute stage of SCI [7]. In addition, several trials of neuroprotective treatments given in the acute phase after SCI have failed [9], while other approaches such as therapeutic hypothermia and administration of drugs targeting inflammation or glutamate excitotoxicity, for example, are still under investigation [8] and are not standard of care. This situation highlights the urgent need for new approaches for preventing secondary damage during the acute phase of SCI.

Emerging evidence suggests that acute-phase hyperglycemia is a critical indicator of poor functional outcomes of SCI [10, 11]. The presence of hyperglycemia (≥126 mg/dl) on hospital admission (irrespective of past diabetes mellitus history) was found to be strongly associated with a lower probability of improvement in motor and sensory functions. Changes to diet might be the least invasive approach to recovery after neurotrauma. A wide variety of evidence suggests that the ketogenic diet (KD) could have beneficial disease-modifying effects in a broad range of neurological disorders [12–16]. The KD is composed of 80–90% fat, with carbohydrate and protein constituting the remainder of the intake. Energy is largely derived from the utilization of dietary fat. These fats are converted in the liver to ketone bodies β-hydroxybutyrate, acetoacetate and acetone, which provide the brain with an alternative energy source to glucose. The ability of a KD to ameliorate the diabetic state and help stabilize hyperglycemia has been repeatedly shown in human studies [17, 18]. In addition, a study by Streijger et al. showed the critical role of ketones in neuroprotection by starting a KD 4 h after cervical hemi-contusion in rats with SCI [19]. Consistent with the published effects of a KD in rat models of SCI and in humans with hyperglycemia, our randomized pilot feasibility trial [20] showed that, compared with a standard hospital diet (SD), 5 weeks of KD improved upper extremity motor scores (Fig. 1).

**Fig. 1 Fig1:**
[figure not shown]
Effects of the ketogenic diet (KETO) versus standard diet (SD) on motor and sensory scores in patients with spinal cord injury. (**a**) American Spinal Injury Association Impairment Scale (AIS) upper extremity motor scores (UEMS) and lower extremity motor scores (LEMS). (**b**) AIS light touch (LT) and pin-prick (PP) sensory scores

Although the exact mechanism by which the KD provides neuroprotection is not fully understood, three main effects on cellular energetics, mitochondria function and inflammation have been suggested to play a key role [21, 22]. Consequently, a KD may be optimal for maintaining a normal glycemic state, promoting inflammation regulation and rescuing mitochondrial function after SCI. Therefore, in this clinical trial, our purposes are to: *i*) show safety and feasibility to administer a KD in the acute stages of SCI; *ii*) determine if 5 weeks of KD versus SD significantly improves motor and sensory function, functional independence, glycemic control, and microbiome composition in patients with acute SCI; and *iii*) quantify serum biomarkers that are linked to improvements in neurological recovery and functional independence via targeted proteomics.

## Research methods/design

### Study design and participants

In a single-masked, longitudinal, randomized, parallel-controlled study design, eligible participants or legally authorized representative (if the participant is under mechanical ventilation) who provide informed consent to the principal investigator (PI) or assigned study coordinator are randomly assigned into a KD intervention group or an SD control group in a 1:1 ratio. Block randomization method with a block size of four is performed by the study statistician. A randomization list is generated, and the random assignments are placed into closed envelopes. All nurses performing blood draws, core facilities and research staff (technicians, students and trainees) analyzing the primary outcomes are blinded to group assignment. A Standard Protocol Items: Recommendations for Interventional Trials (SPIRIT) schedule is presented in Fig. 2 and the SPIRIT checklist is shown as Additional file 1. Outcome measures are performed at three time points: at baseline within 72 h of injury, before discharge from the acute care unit to the rehabilitation hospital, and at discharge from the rehabilitation hospital. Neurological examination via International Standards for Neurological Classification of SCI (ISNCSCI), commonly referred to as the American Spinal Injury Association Impairment Scale (AIS), electrical perception thresholds (EPTs) [23], functional examinations via the Spinal Cord Independence Measure (SCIM) [24, 25], resting energy expenditure (REE) and blood collection (for metabolic, targeted proteomics and safety outcomes) are performed within 72 h of injury, prior to starting enteral feeding (baseline measure). Following acute care, patients are transferred to the University of Alabama at Birmingham (UAB) Spain Rehabilitation Center (SRC) for inpatient rehabilitation care with an average length of stay of 20 days for patients with acute SCI. Accordingly, subsequent examinations are performed prior to transfer to the SRC (rehabilitation measure) and discharge from the SRC at week 5 (discharge measure). A summary of the data collection schedule for the outcomes is shown in Fig. 2, and the flow diagram for the overall study design is shown in Fig. 3.

**Fig. 2 Fig2:**
[figure not shown]
Standard Protocol Items: Recommendations for Interventional Trials (SPIRIT) schedule. *Allocation and baseline testing occur within 72 h of injury; postintervention assessments are performed prior to each patient’s discharge. ^¥^Including cholesterol, triglycerides, high-density lipoprotein cholesterol and calculated low-density lipoprotein cholesterol. ^&^As reflected by liver enzymes, alanine aminotransferase, aspartate transaminase, alkaline phosphatase, albumin, bilirubin and total protein. ^$^Serum fibrinogen, extracellular signal-regulated kinase 1/2, CD11b/CD18 integrin receptor, epidermal growth factor and receptor levels. AIS American Spinal Injury Association Impairment Scale, Wk week

**Fig. 3 Fig3:**
[figure not shown]
Flow diagram for the overall study design. KD ketogenic diet, SCI spinal cord injury, SCIM Spinal Cord Independence Measure, SD standard hospital diet, UAB University of Alabama at Birmingham

The study is currently being conducted at the UAB Center for Clinical and Translational Science, UAB Diabetes Research Center Human Physiology Core, UAB Nutrition and Obesity Research Center Metabolism Core, UAB Microbiome Core and UAB Targeted Metabolomics and Proteomics Laboratory. Participants are considered eligible if they meet the following criteria: 1) are between the ages of 18 and 60 years; 2) have a diagnosis of traumatic SCI at the cervical or thoracic level (C5–T12); and 3) are classified as A (sensorimotor complete), B (sensory incomplete SCI; participants with sensory perception to S4 to S5, but no motor function preserved more than three segments below the cervical neurological level of injury), or C (nonfunctional motor incomplete; sensory and motor function are partially preserved below the neurological level of injury, but more than half the key muscles below the neurological level of injury have a muscle grade strength <3/5) on AIS. The exclusion criteria include: 1) patients with suspected traumatic central cord syndrome, because of the expected substantial spontaneous neurorecovery [26]; 2) pregnant women; 3) neurological (other than SCI), vascular, or cardiometabolic problems (e.g., hypertension or diabetes) that may limit function and interfere with testing procedures; 4) evidence of renal insufficiency or liver disease by history, physical examination and laboratory tests; 5) underlying pulmonary diseases; and 6) evidence of food allergies limiting consumption of a KD. Because of the differences in metabolic responses and nutritional needs among adults and children in the acute stages of traumatic injury, we only focus on adults with acute SCI to determine the effects of a KD on neurological recovery in this study; children (aged <18 years) are not eligible for this study.

The study population is expected to be representative of the demographics of the SCI patient population. Based on 2019 Spinal Cord Injury Facts and Figures, 78% of SCIs reported to the national database have occurred among males [27]. Therefore, we anticipate that, among those who participate in this study, 78% are male and 22% are female. SCI is more common in non-Hispanic white individuals (60.6%), followed by 21.9% in non-Hispanic black individuals, 12.8% with Hispanic origin, 0.7% Native Americans, 2.7% Asian, and 1.3% other; therefore, we expect that more non-Hispanic white individuals compared with other racial or ethnic groups will participate in this study.

### Recruitment

Participants are recruited from the UAB Hospital Trauma, Burns, and Surgical Critical Care (Acute Care) Unit. The PI is responsible for participant recruitment and trial coordination. Screening for the target participant pool is conducted by the UAB Emergency Medicine Research Assistance program. Participants are compensated US$100 for their time.

### Adequacy of the potential participant pool

The primary duty of the UAB Emergency Medicine Research Assistance program is to maintain a presence in the university hospital emergency department on a 24/7 basis. This program provides the research infrastructure necessary to carry out screening and enrollment in numerous clinical trials in the emergency department, which treats 100,000 people per year. The research assistants assist the main research study team in determining patient eligibility by confirming with the existing clinical staff the enrollment inclusion and exclusion criteria. They also notify key research personnel of study enrollment and provide information to the physicians regarding study status, eligibility requirements and general protocol information.

### Interventions/groups

#### The ketogenic diet group

This diet is a high-fat, low-carbohydrate diet (3:1 ratio of fat to carbohydrate and protein) that includes ~75% total energy as fat, ~20% as protein and ~5% as carbohydrate and fiber. Dietary fat sources focus on animal and vegetable (for vegetarians) fats. Dietary fat resources for vegan participants include nuts, seeds, avocados and coconut oil. Dietary protein sources include animal, plant and nut and seed proteins, and dietary carbohydrate resources include vegetarian and vegan sources. KetoCal®, a nutritionally complete, ready-to-feed ketogenic formula in a 3:1 ratio (fat to carbohydrate and protein), is provided by Nutricia for the patients who receive enteral nutrition. Nutricia is a global health company that has been the main provider of KDs for clinical trials, hospitals, health care professionals and communities around the world. Patients who are able to swallow receive liquid or solid high-fat meals that are prepared by the UAB research kitchen, with the overall energy amount determined according to REE assessed via indirect calorimetry and multiplied by an activity factor. REE is measured after a 12-h fast.

#### The standard diet group

Standard enteral tube feeding includes ~45–50% total energy as carbohydrate and fiber, ~30% total energy as fat and ~20% total energy as protein. When patients are able to receive liquid or solid feeding, they are expected to consume ~30% total energy as fat, ~25% as protein and ~45% as carbohydrate based on our preliminary results. Food is provided by UAB main hospital kitchen, and patients are allowed to choose options from the standard hospital menu, with the overall energy amount determined according to REE assessed via indirect calorimetry and multiplied by an activity factor.

REE measurements are performed in the patient’s hospital room. Participants lie supine on a comfortable bed with the head enclosed in a plexiglass canopy. After resting for 15 min, REE is measured for 30 min with a portable computerized, open-circuit, indirect calorimetry system with a ventilated canopy (Vmax ENCORE 29 N Systems; SensorMedics Corporation, Yorba Linda, CA, USA). Oxygen uptake and carbon dioxide production are measured continuously and values are averaged at 1-min intervals, and the REE is calculated from these data. The last 20 min of measurement is used for analysis.

### Inpatient rehabilitation care

Patients in both groups undergo an intensive rehabilitation program for about 5 weeks. Therapy is offered 5 days (a total of 15 h) per week. The standard of care for both groups includes: respiration therapy, bed mobility, transfers, wheelchair mobility skills, bowel and bladder management, tone and spasticity management, and skills for performing other activities of daily living. Rehabilitation protocols and treatment hours are recorded for each patient. The average duration of stay in the SRC is 30 days for individuals with tetraplegia (injury level C4–C7) and 21 days for individuals with paraplegia (injury level T1–S5).

## Outcome measures and analysis

The primary outcomes are as follows: 1) safety via biomarkers of systemic inflammation (C-reactive protein), lipids (total cholesterol, high-density lipoprotein cholesterol, low-density lipoprotein cholesterol and triglycerides), sodium, liver enzymes (alanine aminotransferase, aspartate transaminase, alkaline phosphatase, albumin, bilirubin, total protein, nutritional ketosis (β-hydroxybutyrate) and glycemic status (fasting blood glucose and insulin)); 2) neurological recovery (AIS) motor and sensory scores and EPTs; 3) functional independence (SCIM); 4) microbiome composition; and 5) serum biomarkers (targeted proteomics).

In compliance with goals of the National Institute of Neurological Disorders and Stroke common data elements initiative, we are utilizing portions of the SCI common data elements that are expected to increase the efficiency and effectiveness of our clinical research study and diet intervention, increase data quality, and facilitate data sharing and comparisons across studies. For data analyses and results reporting, we adhere to the guidelines for reporting results using the international spinal cord core dataset [28].

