### Minimally acceptable intervention adherence rates

Adherence to diet will be closely monitored by the study team by measuring serum β-hydroxybutyrate levels once a week. A blood concentration of 0.5–3 mM (nutritional ketosis) will be considered safe and acceptable. Adherence will also be assessed using food records. The food record will be a simple checklist to indicate that supplied foods were consumed, with space to add the quantity of consumption and any deviations from the protocol. In addition, the study dietician will communicate directly with each participant at least weekly to improve adherence.

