### Clinical procedures to measure safety

Fasting blood samples are collected to determine the levels of biomarkers of systemic inflammation, lipids, sodium, liver enzymes and glycemic status. In addition, blood samples are collected for measurement of blood ketone (β-hydroxybutyrate) levels three times a week, 2 h after the first meal of the day, to confirm nutritionally induced ketosis (blood concentration 0.5–3.0 mM) in the KD group. All serum samples will be obtained in the UAB Hospital Acute Care Unit and then stored in freezers within the PI’s ([name]) research laboratory at −80°C until analyzed by core personnel. Levels of sodium, β-hydroxybutyrate, lipids, C-reactive protein, glucose and insulin are assessed via enzymatic assays in the Diabetes Research Center Human Physiology Core. The concentration of low-density lipoprotein cholesterol is calculated using the Friedewald formula. In addition, levels of liver enzymes are measured via enzymatic assays at the UAB Hospital Outreach Laboratory.

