### Statistical analysis

Statistical analyses for neurological recovery will include comparisons of means of motor and sensory function, functional independence and serum measurements (e.g., glucose, insulin, alanine aminotransferase and aspartate transaminase) between the two groups, as well as comparisons within each group of the changes from baseline to rehabilitation to discharge (which should take approximately 5 weeks). Descriptive statistics, including measures of central tendency (sample mean, sample median) and dispersion (variance) will be calculated for each group. For safety outcomes, instead of comparing the two groups to the established standard safety values, we will compare circulating levels of proposed outcomes at the various time points among the two groups. If there are no significant group differences in these outcomes, we will conclude that the KD intervention is safe. We will also calculate 95% confidence intervals for the mean group differences for these outcomes as an additional check on safety and feasibility. The primary method of analysis will be analysis of covariance (ANCOVA), regressing the 5-week outcomes (safety, motor and sensory recovery, functional independence, and glycemic state) on the randomly assigned diet, baseline values of the measures, and other covariates such as age and sex. Repeated measures ANCOVA will also be used. Statistical assumptions will be assessed using box plots, residual plots and normal probability plots. Secondary analyses, accounting for all time points, will be conducted using mixed linear models, including repeated measures models. An appropriate structure for the covariance matrix (e.g., the unstructured covariance matrix) will be selected for these models using the final data. When a model term is statistically significant, the Tukey–Kramer multiple comparisons test will be used to determine which specific pair of means are significantly different. This method will allow us to compare changes over time (within-group changes) and differences between groups simultaneously. Covariates (e.g., length of enteral and solid feeding and length of stay in acute and rehabilitation care) will be accounted for in these analyses. Overall cross-sectional between-group comparisons, such as baseline comparisons used to examine pretest parameters, may be performed using the two-group *t* test, and overall within-group comparisons may be performed using the paired *t* test. If assumptions of normality of distribution for the above tests are not tenable, variables may be transformed prior to analysis, or appropriate nonparametric tests, such as the Wilcoxon rank-sum and signed-rank tests, may be used. Statistical tests will be two-sided and will be performed using a 5% significance level. Stratified analyses accounting for different injury levels will also be performed. These analyses will be specific to the distribution of data in each individual subgroup, which will minimize heterogeneity and allow us to analyze subgroups that may be more statistically homogenous and clinically relevant. SAS software, version 9.4 or later, will be used to conduct the statistical analyses. Multiple imputation methods will be used to address missing data for variables with moderate amounts of missing data (≥10%) and after examining whether data are missing completely at random, missing at random, or missing not at random. Missing data analysis will not be performed on variables with <10% missing data to avoid statistical bias larger than that obtained through the use of complete case analysis.

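### β-hydroxybutyrate sits in the safety set judged by no significant group difference, so a ketogenic diet delivered as planned cannot be expected to meet the only stated criterion for safe; fasting glucose and insulin are classified inconsistently

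*Protocol article*

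**What the plan says.** Four parts of the protocol article bear on this point.

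- **Outcome measures and analysis.** Primary outcome 1 is safety. Its list runs through C-reactive protein (CRP), lipids, sodium and the liver panel to "nutritional ketosis (β-hydroxybutyrate) and glycemic status (fasting blood glucose and insulin". A misplaced bracket nests the last items under liver enzymes, but on either reading they belong to the safety outcome.
- **Statistical analysis.** Safety markers are compared between KD and the standard diet (SD) "instead of comparing the two groups to the established standard safety values". The criterion follows: "If there are no significant group differences in these outcomes, we will conclude that the KD intervention is safe". Confidence intervals (95%) for the mean group differences are added as a further check, without a margin or a direction.
- **Minimally acceptable intervention adherence rates.** Serum β-hydroxybutyrate is the adherence measure: "A blood concentration of 0.5–3 mM (nutritional ketosis) will be considered safe and acceptable". Clinical procedures to measure safety says that ketones are drawn "to confirm nutritionally induced ketosis (blood concentration 0.5–3.0 mM) in the KD group". The same section lists glycemic status with the safety biomarkers.
- **Glycemia as a goal.** The Abstract states the aim to "determine if consuming 5 weeks of a KD significantly improves motor and sensory functions, functional independence and glycemic control", and the Background repeats it. The main ANCOVA is described as "regressing the 5-week outcomes (safety, motor and sensory recovery, functional independence, and glycemic state"), which lists glycemic state beside safety. The proteomics correlations in the same section separate the two again.

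**The concern.** A between-group test on β-hydroxybutyrate asks whether the two diets produced different ketone levels. In this trial they are supposed to. A significant difference shows that KD was delivered, yet the same result stops the only route the protocol gives to the conclusion that KD is safe. Poor adherence would make that conclusion easier to reach.

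Glucose and insulin raise a related problem. If they are safety markers, a significant difference blocks the safe conclusion. If they are efficacy markers, a significant improvement is what the trial hopes for. The protocol supports both readings, so one p-value could be read in two directions.

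Safety is the first stated goal and the first primary outcome, so the trial needs a safety conclusion that can be interpreted whether or not the diet worked.

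**Working it through.** **Inputs from the protocol article.** 24 completers per group (Power calculations); two-sided tests at 5% (Statistical analysis); 15 safety markers in primary outcome 1, namely CRP 1, lipids 4, sodium 1, liver panel 6, β-hydroxybutyrate 1, glucose 1, insulin 1.

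**Inputs that are assumptions.** The article gives neither an SD nor an expected group difference for ketones. I took differences of 0.5 and 1.0 mM and between-patient SDs of 0.3 to 0.7 mM.

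**Formula.** Two-group t test with n per group, difference Δ and SD σ: df = 2n − 2 = 46, critical t = 2.013, noncentrality = (Δ/σ)·√(n/2) = (Δ/σ)·√12. Power is the probability that a noncentral t variable with these values exceeds 2.013 in absolute size.

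**Check on the plan's own figures.** Motor score: 19.5/23.5 = 0.830, noncentrality 2.874, power 80.3%. Light touch: 27.3/33 = 0.827, noncentrality 2.866, power 80.1%. Both agree with the stated 80%, so the method matches the plan's. No power figure is stated for any safety marker.

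**β-hydroxybutyrate, probability of a significant group difference**

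| Difference | SD 0.3 mM | SD 0.5 mM | SD 0.7 mM |
|---|---|---|---|
| 0.5 mM | >99% | 92% | 68% |
| 1.0 mM | >99% | >99% | >99% |

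For example, 0.5/0.7 = 0.714, noncentrality 2.474, power 68%.

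**Delivered against undelivered diet.** As an illustration only, treat the 15 markers as independent, each with one unadjusted 5% test. (They are not truly independent; LDL cholesterol, for one, is calculated by formula.)

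- KD changes nothing: the chance of no significant difference is 0.95^15 = 46%.
- KD raises ketones and changes nothing else: the chance is 0.95^14 × (1 − power) = 0.488 × (1 − power). At 68% power this is 0.488 × 0.32 = 16%; at 92% it is 0.488 × 0.08 = 4%; above 99% it is under 0.5%.

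Successful delivery alone therefore cuts the chance of meeting the criterion from 46% to 16% or less under these assumptions.

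**Glucose and insulin.** No SDs or expected effects are given, so only standardised effects can be used. Power per marker is 17% at 0.3 SD, 40% at 0.5 SD, 77% at 0.8 SD and 92% at 1.0 SD. A significant difference is possible but not assured.

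**The case against.** A reader might infer that KD can be called safe only if participants were not in ketosis, or that a working diet would be declared unsafe. The text does not support either. It gives a condition that leads to the conclusion safe; it does not say that this is the only route, nor what a significant difference would mean. The adherence section also calls 0.5–3 mM safe in its own right. What stands is narrower: the single criterion that is stated is one a ketotic KD arm cannot be expected to meet, and nothing is said about the alternative.

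The adherence section does already give ketones a separate role with an absolute range. That supports the remedy, but no sentence takes ketones out of the between-group comparison, and the analysis section expressly sets standard safety values aside.

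For glucose and insulin, the Statistical analysis section twice lists glycemic status apart from safety. This objection has force: their role is unsettled, and the plan does not show that they must fall under the safety criterion. Two other sections still place them there, so they need reconciling.

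The confidence intervals do not help with ketones. Without a margin or direction, they would simply confirm the intended difference.

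Participant protection does not rest on this criterion, since quarterly committee review and adverse event reporting are provided for separately. What is affected is the trial's reported safety conclusion. A separate analysis plan might settle the matter, but the article itself states both the classification and the criterion, and they conflict.

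**Conclusion.** The point holds for β-hydroxybutyrate, and the conflict needs no calculation: the outcome list and the safety criterion ask for no difference on a marker that the diet is given to change, within a range the protocol itself calls safe. On assumed SDs of 0.3–0.7 mM and 24 per arm, a 1.0 mM separation is significant with probability above 99%, and a 0.5 mM separation with 68% to over 99%. It would go too far to say that a compliant arm almost surely misses the criterion at every plausible separation: at 0.5 mM and SD 0.7 mM the chance from ketones alone is about two in three.

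For fasting glucose and insulin the finding is an inconsistent classification. The power figures for ketones do not carry over to them.

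**What to change.** 1. Remove β-hydroxybutyrate from the between-group safety comparison. Analyse it as adherence or exposure in the KD arm against the protocol's own 0.5–3 mM range: the proportion within range with an exact confidence interval, and readings outside the range reported descriptively. Because repeated readings on one person are correlated, base the exact interval on participants. The sections also differ on how often ketones are measured (weekly in one, three times a week in the other), so this must be reconciled before the denominator is set.
2. Classify the between-group comparisons of fasting glucose and insulin as glycemic efficacy, consistently in the outcome list, the safety procedures and the analysis.
3. For the remaining markers, read differences by direction of harm. This matters for CRP, which the diet may lower, since the Background and Discussion expect an anti-inflammatory effect.
4. State what will be concluded when the criterion is not met. Any safety limits are for the investigators to set.
5. Reconcile Outcome measures and analysis, Minimally acceptable intervention adherence rates, Clinical procedures to measure safety, and Statistical analysis.

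The cost is wording, best settled before any comparative results are seen. No new data are needed and no power is lost. The change does not cure the separate problem of inferring safety from non-significance in the remaining markers: at 24 per arm, a true shift of 0.5 SD would be missed about 60% of the time (100% − 40%).
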